## Discussion

The project results will provide very useful information on the degree of registration and performance of the 7 preventive services selected. These 7 activities have been widely implemented and have a high impact on the health of our population [2-6]. The large population database of the study, with more than 850,000 people recorded, will increase considerably the external validity of the results and will reflect usual clinical practice at the Primary Care settings in the Spanish NHS.

This fact may help to overcome the current limitations and to investigate CPV and the factors that have an impact on the implementation of preventive services.

Certainly the source of information used and the ECRs may have limitations. The heterogeneity of current computer systems may complicate the extraction of outcomes and of variables. However, the design of the data extraction interfaces and data transfer will minimize the problems. The lack of exhaustivity in data recording may introduce some distortions in the information. Nevertheless, stability of computer systems at the centres will help to minimize this problem and the quality control measures will help to identify the magnitude of the problem.

Studies based on cluster sampling allow important reduction in costs and greater easiness in administration but require knowledge of the ICCs. For this study ICCs has been estimated from studies conducted in other countries. In our study we will provide information concerning the magnitude of the ICC, evaluate factors that influence their magnitude, estimate within-cluster and between-cluster components of variance for the outcome measures under consideration and determine the sample size; all of these factors will aid the design and statistical analysis of future cluster-based studies set in PC.

In conclusion, the present study will provide new knowledge in:

- The identification of factors related to the variability in the implementation of preventive services, which will facilitate the design of strategies for improvement in the planning and administration of services in PC.

- The assessment of the evolution of the detected health problems will improve the degree of existent evidence taking into account the results of screening and the control of those problems. This will be very useful for the evaluation of the PAPPS and other studies based on this source of information.

- The estimation of the ICC will be of considerable help in the design, calculation of sample size and analysis of future studies based on the randomisation of clusters in our environment.

- Finally, although not being an aim of the project, information will be obtained on the characteristics of the different computer systems and this information will generate recommendations for the standardization of systems for future applications.

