### Sources of information in Primary Care: the computerization of clinical records

Primary Care uses electronic clinical records (ECRs) to monitor health problems and to register preventive care services. Although information collection intends to be comprehensive, the ECR systems are different for each region.

Routinely-collected data have undisputed advantages in the study of CPV; they are available almost instantaneously and provide information on a large number of patients. The creation of registries or databases of health-care interest in PC was given a considerable boost with the computerization of clinical records. Spain, contrary to other countries [19-23], has little experience in the use of nation-wide databases containing electronic clinical records in PC. Recently, projects such as the BIFAP project in pharmacoepidemiological research [24] have been initiated in Spain.

However, there are certain difficulties in their use: 1) The data was originally collected for a function different from current research requirements; 2) ECR systems are different in each region, with different standards and computer programs; 3) The heterogeneous degree of implementation in PHCTs; and 4) The degree of exhaustivity of data recorded (for example, some activities are carried out but are not registered). Nevertheless, the potential of this type of registry has been confirmed by different European experiences mentioned earlier [25-27]. As such, the advantages associated to computerization of clinical records are beginning to be appreciated by the different regions and the richness of information provides enormous potential for the study of CPV in primary care.

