#### Quality control

Quality controls will be carried out in the 2 extractions of data comparing agreement between the central database and the original data of some centres as for: number of patient, visits and diagnoses as well as data of prevalence of certain diseases. It will also be checked if the population data is appropriate by comparing it with data from the census and other official sources. In the case of items related to clinical activities (for example blood pressure measurement), any register with missing values will be considered as not performed.

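### The quality control checks cannot size the under-recording of the seven services, as the Discussion suggests, and unrecorded or lost entries count as non-performance in objective 1

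*Protocol article*

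**What the plan says.** The article names the risk twice. The Background section on sources of information lists, among the difficulties of routine data, "The degree of exhaustivity of data recorded (for example, some activities are carried out but are not registered". The Discussion returns to it: "The lack of exhaustivity in data recording may introduce some distortions in the information". It then offers two reassurances. One is that computer systems at the centres are stable. The other is that "the quality control measures will help to identify the magnitude of the problem".

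The Quality control section describes the measures. At both extractions the study will be "comparing agreement between the central database and the original data of some centres as for: number of patient, visits and diagnoses", and also on the prevalence of certain diseases. Population data will be compared with the census and other official sources. For clinical activities, with blood pressure measurement as the example, "any register with missing values will be considered as not performed".

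The outcome definitions for objective 1 rest on information or a registry entry being present. The objective itself is worded as variability in performance, and the Discussion promises results on "the degree of registration and performance of the 7 preventive services selected".

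**The concern.** A field for one of the seven services can be empty for three reasons: the service was not delivered, it was delivered but not entered, or it was entered but lost between the regional system and the central database. The scoring rule treats all three alike. That is workable if the second and third can be sized separately, and the Discussion gives the reader to understand that quality control will help with the second. If the listed checks cannot do so, a team that records poorly looks the same as a team that screens poorly.

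This affects how objective 1 is read. The results are meant to guide strategies for improving services, and poor recording calls for a different remedy from poor delivery. It also affects what the objective 3 ICCs describe.

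**Working it through.** **Step 1: set the checks against the risk.** The plan states no figure for recording completeness, so there is none to reproduce. The test is whether each listed check could reveal a service that was delivered but never entered.

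| Check (Quality control) | Comparator | Items | Service never entered | Service field lost in extraction |
|---|---|---|---|---|
| Agreement | Original data of some centres | Patients, visits, diagnoses, disease prevalence | No: absent on both sides | No: service fields not listed |
| Population | Census, other official sources | Population data | No: not a service item | No |

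Individual data come only from the electronic clinical records (Information source). On the natural reading, the centres' original data are those same records, so an entry never made is missing from both sides and agreement can be complete. If the original data meant something wider, the listed items still include none of the seven services.

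**Step 2: follow the empty field.** Under the scoring rule it becomes a service not done. Under the outcome definitions it enters the numerator of objective 1 as a failure.

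**Step 3: illustrate the possible size.** All completeness values here are assumptions. Let every team deliver the service to the same proportion P of patients, and let completeness have mean c and between-team SD s.

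- Registered rate: p = P × c
- Between-team SD from recording alone: P × s
- ICC from recording alone: (P × s)² / [p(1 − p)]

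Two teams, P = 0.90, completeness 95% and 75%: 0.90 × 0.95 = 0.855 and 0.90 × 0.75 = 0.675, a gap of 18 points with identical practice.

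Many teams, P = 0.90, c = 0.85: p = 0.765 and p(1 − p) = 0.1798.

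- s = 0.10: 0.0081 / 0.1798 = 0.045
- s = 0.05: 0.002025 / 0.1798 = 0.011

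The next table takes P from the earlier programme evaluations cited in the Background (more than 70% for one group of services, 92.8% for the other) and c from 0.7 to 0.9:

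| SD of completeness | ICC, P = 0.70 | ICC, P = 0.928 |
|---|---|---|
| 5 points | 0.005 | 0.010 to 0.016 |
| 10 points | 0.020 to 0.021 | 0.038 to 0.063 |
| 15 points | 0.044 to 0.047 | 0.085 to 0.141 |

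For scale, the planning ICC under Sample size and randomisation is 0.05. Depending on the assumed spread, the contribution of recording runs from a tenth of that value to more than twice it. The listed checks could not show which applies.

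**The case against.** The other side has real force on several points.

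- **The claim is hedged.** The article says the measures will help to identify the magnitude, in a paragraph on limitations. A reader might infer that it promises a full measurement of under-recording; it does not. Even so, the listed checks give no help on this quantity for the seven services.
- **Not every check looks inward.** A reader might infer that all quality control compares the records with themselves. The census comparison is external, but it concerns population only.
- **The design limits the problem.** Teams must have been computerized before 2005, must use the electronic record widely, and need agreement from more than 80% of their professionals (Study population). Record system, its starting year and experience with it are covariates (Other measures). These may narrow or partly adjust for recording differences. They do not measure them. System is also fixed within region (OMI-AP in Navarra and Aragón, eCAP in Catalonia), so it cannot adjust for anything in the regional analyses.
- **The outcomes are defined by registration, and the scoring rule is disclosed.** This is correct, and it is why most of the remedy is wording. The mismatch lies in the word performance in objective 1 and the Discussion.
- **The ICCs remain useful.** A reader might infer that objective 3 is invalidated. It is not: a future study using recorded outcomes needs the ICC of the recorded outcome, recording variation included.
- **An article condenses.** A fuller protocol may list more checks. If it contains an independent check of the services, citing it would answer the point. As printed, the Discussion relies on measures that do not support the statement.

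**Conclusion.** The point holds as a mismatch between a stated safeguard and the checks described. None of the listed checks can size the under-recording of the seven services, none is stated to detect extraction loss on those fields, and both are scored as non-performance in objective 1. This follows from the text and needs no assumption about completeness, although the agreement check can be called blind to unentered services only if the original data are the electronic records or the item list is as printed.

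The size is unknown. The 18-point gap and the ICCs of 0.011 to 0.045 show what assumed completeness values would produce. They are not estimates for these regions, and the entry criteria should pull the spread down. The documents do not support concluding that the observed variability will be mainly a recording effect. They support only that the listed checks could not tell.

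**What to change.** 1. **Discussion and objectives.** Replace the statement about magnitude with wording such as: *quality control verifies extraction and population coverage; it does not quantify activity that was never recorded.* Word objective 1 and its conclusions as variability in registered implementation, and describe the ICCs as ICCs of recorded outcomes.
2. **Quality control.** Add the seven service fields, as counts and proportions recorded per team, to the agreement check already planned for both extractions. Extraction loss on the primary outcomes is then detected before a missing item is scored as not done. This does not detect services never entered, and the text should say so.

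The cost is a more modest headline claim and a little more checking work.

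A per-team completeness indicator, such as the share of attended patients with diagnosed hypertension who have any blood pressure recorded, could be shown as a descriptive figure. It should not be used to adjust the models or to exclude teams. A missing value there is just as ambiguous between not done and not recorded, so either use could remove the real practice variability that objective 1 sets out to describe.
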